## 2.2 Model Development

We evaluated data from 111,352 admissions to Vanderbilt Children's Hospital from 1/1/2010 to 10/31/2017. Cases were identified from ICD9/10 codes and a subset of these records were reviewed for accuracy. Potential covariates were identified from known pediatric risk factors for VTE development prior to data collection, and the corresponding clinical data were electronically extracted through the Vanderbilt Research Derivative. Logistic regression was used to test the association of potential risk factors with development of VTE. Variable inclusion in the final model was based on data reduction methods including univariate analysis significance, availability in routine medical records, clinical expertise, and assessment of collinearity between variables. The model was validated using an internal bootstrap calibration.

We identified 110,537 controls and 815 cases within the cohort. The most significant variables for developing VTE were a history of thrombosis (OR 8.7, 95% CI 6.6 – 11.3,  $p < 0.01$ ), presence of a central venous line (OR 4.9, 95% CI 4.0 – 5.8,  $p < 0.01$ ), and cardiology consultation (OR 4.0, 95% CI 3.3 – 4.8,  $p < 0.01$ ). Additional significant variables included whether a blood gas was performed, whether the patient had an infectious diseases consultation, patient age, mean corpuscular hemoglobin concentration (MCHC), red cell distribution width (RDW), and lactate. We selected these 11 final variables for use in the model, which yielded excellent discriminatory power (C-statistic = 0.907 in the model development cohort).

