### **6.2 Intervention Arm**

Patients in the intervention arm will have their VTE risk prediction scores presented to the study team daily on weekdays via Epic report, which will list patients in descending order of risk severity for review by the VTE research team each weekday. Starting with the highest risk patients, the VTE research team will review each patient and clinical situation, and then the VTE research team will directly discuss risks/benefits

of prophylactic anticoagulation with the admitting team. Patients with a risk score  $<2.5\%$  will not be reviewed, and we anticipate most of the intervention arm patients will fall into this category (based on our previous data, we anticipate  $>90\%$  of all patients will score  $<2.5\%$ ). The VTE risk report will be re-calculated based on updated EHR data every day at midnight.

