### **6.3 Control Arm**

Patients randomized to the control arm will continue to receive Vanderbilt Children's Hospital standard of care anticoagulation practice, which is at the discretion of the admitting team. In general, nearly no pediatric patients are offered prophylactic anticoagulation unless a previous VTE has been identified. This currently is at the discretion of the provider and no risk scoring is used. VTE risk prediction scores will be calculated and stored for analysis, these will not be visible to the study team in real time.

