## 10 Statistical Considerations

### 10.1 Statistical Analysis Plan

Primary analyses will be conducted at the encounter level, while secondary analyses will be conducted at the patient level (patients can potentially experience multiple encounters during the study period).

The rate of VTE events (primary outcome), the proportion of patients receiving prophylactic anticoagulation (secondary outcome), and the rate of bleeding-related adverse events (secondary outcome) will be compared between the intervention and control arms using unadjusted risk differences with 95% confidence intervals. We have not specified *a priori* any adjustment variables to include in multivariable models. Any variable with a clinically meaningful imbalance between the intervention and control groups will be adjusted for in multivariable regression models; given the large sample size we do not anticipate any such imbalances. For the primary outcome, a two-sided p-value (obtained from Pearson's chi-square test) of  $< 0.05$  will indicate statistical significance. Secondary subgroup analyses will be performed by patient gender, risk of VTE, primary diagnoses, surgical vs. nonsurgical, and consultants involved.

Primary analyses will be conducted by intention-to-treat; secondary analyses will be as treated, considering whether treatment recommendations were followed by the admitting team. Secondary as-treated analyses will be performed among the strata of high-risk patients (predicted probability  $\geq 0.025$ ) randomized to usual care, to the intervention but treatment recommendations were not followed, and to the intervention and treatment recommendations were followed.

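### Covariates are chosen by observed imbalance while the stored admission risk score is left out of the primary analysis, and no intention-to-treat comparison is named at the 2.5% review threshold

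*Protocol*

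**What the plan says.** Section 10.1 of the protocol states that the primary outcome, with two secondary outcomes, "will be compared between the intervention and control arms using unadjusted risk differences with 95% confidence intervals". Significance is judged as follows: "For the primary outcome, a two-sided p-value (obtained from Pearson's chi-square test) of" less than 0.05. The analysis set is all randomized encounters: "Primary analyses will be conducted by intention-to-treat".

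On covariates, the section says that it has not specified in advance "any adjustment variables to include in multivariable models", and then sets a rule: "Any variable with a clinically meaningful imbalance between the intervention and control groups will be adjusted for in multivariable regression models". It adds that such imbalances are not expected at this sample size.

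The risk score is calculated in both arms, first at admission (section 6.1). For controls, "VTE risk prediction scores will be calculated and stored for analysis" (section 6.3). Section 2.2 describes the model as one "which yielded excellent discriminatory power", with a C-statistic of 0.907 in the development cohort. In the intervention arm, patients scoring below 2.5% "will not be reviewed, and we anticipate most of the intervention arm patients will fall into this category" (section 6.2); the expected share is above 90%, and scores are refreshed every midnight.

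The score enters section 10.1 in two places only: VTE risk is one of five subgroup factors, without a cut-point, and an as-treated analysis covers patients with a predicted probability of at least 0.025.

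**The concern.** Two features of section 10.1 fit the design poorly.

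First, under randomization an observed imbalance is a chance event. A rule that adjusts for whatever looks imbalanced picks covariates after the data are seen. The protocol lists no candidate variables, sets no threshold for a meaningful imbalance, and does not say which estimate prevails if the adjusted and unadjusted results differ. A strong baseline predictor is available in every patient and could have been named.

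Second, the intervention works through review, and review starts only at a score of 2.5%. Patients who stay below it are managed alike in both arms, so their events dilute the overall contrast. The sample-size section never states how large an effect among reviewed patients its overall target implies. Those patients include some with contraindications and some whose admitting team does not follow the recommendation. The analysis that isolates the high-risk group is split by whether recommendations were followed, so it is not a randomized comparison.

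At stake are the credibility of any adjusted estimate and the chance of seeing an effect in the patients on whom the tool acts.

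**Working it through.** **Inputs from the protocol.** Two-sided alpha 0.05; 1% versus 0.595%; 7,500 per arm at the minimum, 22,500 at the maximum (section 10.2). Review at a score of 2.5% or more, expected in under 10% of patients (section 6.2). C-statistic 0.907 (section 2.2). Historical rate 815/111,352 = 0.73% (section 2.2).

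**Assumed, because not given.** s, the share of VTE events in patients scoring at least 2.5%, and h, the share of patients in that group. A calibrated score with logit-normal risk and a 1% event rate gives:

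| C-statistic | h | s | variance explained by score |
|---|---|---|---|
| 0.907 | 8.6% | 0.67 | 10.8% |
| 0.85 | 9.2% | 0.54 | 5.0% |
| 0.80 | 8.8% | 0.43 | 2.6% |

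The range of s examined below is 0.43 to 0.90.

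**1. The plan's own figure.** Power = Φ{[|p1 − p2|√n − 1.96√(2p̄(1 − p̄))] / √[p1(1 − p1) + p2(1 − p2)]}, with p̄ the mean of p1 and p2. With p1 = 0.01, p2 = 0.00595, p̄ = 0.007975 and n = 7,500: (0.3507 − 0.2465)/0.1258 = 0.829, and Φ(0.829) = 79.6%. The stated 80% reproduces.

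**2. Effect implied in reviewed patients.** The overall relative reduction is 1 − 0.595 = 40.5%. If it comes only from reviewed patients, they need 0.405/s.

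| s | 0.5 | 0.6 | 0.67 | 0.8 | 0.9 |
|---|---|---|---|---|---|
| Reduction needed | 81% | 68% | 60% | 51% | 45% |

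**3. Pooled test against the stratum test.** Suppose that reviewed patients have a 40.5% reduction, the rest have none, and h = 10%. The pooled test compares 0.01 with 0.01(1 − 0.405s) at 7,500 per arm. The stratum test compares 0.01s/h with 0.595 times that rate at 7,500h = 750 per arm. At s = 0.67 these are 1% versus 0.729%, and 6.7% versus 3.99%.

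| s | Pooled | Stratum | Difference (points) |
|---|---|---|---|
| 0.43 | 20% | 46% | 26 |
| 0.5 | 26% | 52% | 26 |
| 0.6 | 36% | 60% | 24 |
| 0.67 | 43% | 65% | 21 |
| 0.8 | 59% | 73% | 14 |
| 0.9 | 70% | 78% | 8 |

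At s = 0.67, 80% power needs about 18,300 randomized per arm with the pooled test and about 10,800 with the stratum test. At the permitted 22,500 per arm, the pooled test reaches 87% at s = 0.67 but 62% at s = 0.5.

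**4. What score adjustment gains.** Simulation of 1,500 trials per scenario, 7,500 per arm, 1% rate, 40.5% effect confined to scores of at least 2.5%:

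| C-statistic | Chi-square | Score-adjusted logistic | Stratum chi-square |
|---|---|---|---|
| 0.907 | 45% | 47% | 66% |
| 0.80 | 20% | 20% | 46% |

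Type I error was about 5% for all three. Across the scenarios examined, adjustment adds about 0 to 5 points.

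**The case against.** The strongest reply is that the primary analysis is sound as it stands. The p-value comes from an unadjusted chi-square fixed in advance. A reader might infer that the imbalance rule lets hindsight into the significance decision. It does not, because the rule reaches only the additional adjusted estimates. The pooled intention-to-treat test also answers the question in section 3, which is whether VTE falls across the institution. Dilution is the price of that question and not an error.

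A reader might also infer that ignoring the score as a covariate is what costs the power. The figures do not support that: adjustment gains very little at a 1% event rate, and 0.907 is a development-cohort value. The larger contrast comes from pooling, and adjusting the primary analysis does not recover it.

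Nor do the documents support the reading that over 90% of patients cannot receive the intervention. That share is an expectation, and nightly rescoring means that a patient below 2.5% at admission can cross later and be reviewed.

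Finally, section 10.2 allows up to 45,000 patients. With a 50% effect in reviewed patients at C = 0.907, pooled power is about 41% to 62% at 7,500 per arm (event rates 0.73% and 1%) and about 85% to 98% at 22,500.

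All of this stands. It leaves two gaps: a data-driven covariate rule that the protocol itself fixes, and no named intention-to-treat comparison at the threshold where the tool acts. The subgroup by VTE risk has no cut-point and no priority over four others.

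**Conclusion.** The point holds as a recommended improvement; it does not invalidate the trial. The imbalance rule should go because it makes adjusted estimates depend on the observed data when an obvious baseline covariate exists. The benefit is mainly one of credibility, since the gain in power is about 0 to 5 points depending on the true C-statistic.

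The second part is larger but conditional. For an effect confined to reviewed patients, an intention-to-treat comparison among those scoring at least 2.5% has about 8 to 26 points more power than the pooled test at 7,500 per arm. This rests on assumed event shares of 0.43 to 0.90, a 40.5% effect in those patients, a 1% overall rate and about 10% of patients in the stratum. The protocol does not give the event share. The figures treat the score as one value per patient, so they do not directly evaluate a stratum defined by first crossing during the stay. The gain belongs to a secondary analysis; the power of the primary test stays nearly the same.

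**What to change.** 1. In section 10.1, delete the imbalance-triggered rule. Pre-specify the primary all-encounter intention-to-treat risk difference as adjusted for the admission VTE risk score (logistic regression with standardization), with the unadjusted risk difference as support.

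2. Name as leading secondary analysis the intention-to-treat comparison of arms among encounters whose score reaches 2.5%, defined identically in both arms. There are two options:
   - The admission score, which is simple but misses later crossings.
   - The first crossing, with VTE counted only from that point. Within an encounter, care does not differ by arm before the score crosses, so the comparison stays randomized. Earlier encounters of the same patient could carry over, so repeat it in first encounters as a sensitivity check.

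3. If first crossing is used, state in section 6.3 that the nightly score is stored for controls too; that section does not say how often it is kept.

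4. In section 10.2, state the reduction among reviewed patients that the overall target implies, with the event share taken from the development cohort.

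The cost is analysis wording, a slightly more complex primary model and storage of nightly control scores. Enrolment and patient care are unchanged.

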### **5.2 Randomization**

Patients will be randomized 1:1 to the intervention or control arms upon admission via an automatic process built into the electronic health record. Both arms will continue to receive local standard of care practice for VTE prophylaxis.

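### The secondary as-treated strata split the intervention arm after randomization and leave usual care whole, so they can show a spurious benefit or hide a real one

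*Protocol*

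**What the plan says.** Section 10.1 of the protocol sets the analysis sets: "Primary analyses will be conducted by intention-to-treat; secondary analyses will be as treated", the latter "considering whether treatment recommendations were followed by the admitting team". It then fixes the as-treated comparison: "Secondary as-treated analyses will be performed among the strata of high-risk patients" (predicted probability of at least 0.025), in three groups, those "randomized to usual care, to the intervention but treatment recommendations were not followed, and to the intervention and treatment recommendations were followed".

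Other sections give the timing and the selection:

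- Section 5.2: "Patients will be randomized 1:1 to the intervention or control arms upon admission".
- Section 6.2: the research team reviews intervention patients on weekdays, from the highest risk down, and discusses prophylaxis with the admitting team. The risk report "will be re-calculated based on updated EHR data every day at midnight".
- Section 7: children with severe bleeding disorders, significant hemorrhage or severe renal dysfunction would not be considered for anticoagulation.
- Section 10.1: no adjustment variables are named in advance. Adjustment is foreseen only for imbalance between the intervention and control groups.

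Section 10.1 also lists subgroups: "Secondary subgroup analyses will be performed by patient gender, risk of VTE, primary diagnoses, surgical vs. nonsurgical, and consultants involved". It does not say when these factors are measured.

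**The concern.** Randomization makes the two arms comparable. It does not make part of one arm comparable with the whole of the other. Whether a recommendation is followed is decided by the admitting team, after review and in the light of the child's condition. No matching split exists among controls, whose counterparts to the followed and the not-followed patients remain mixed together.

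Three features follow from the text:

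1. **Selection on prognosis.** The reasons for acting or not acting on advice may themselves be related to VTE risk.
2. **Time before action.** A child who has a VTE before advice to start prophylaxis is acted on cannot be counted as having had it followed. The same early event counts in usual care.
3. **An incomplete classification.** A high-risk intervention patient with no recommendation belongs to neither intervention group.

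This is the protocol's VTE comparison aimed at whether acting on the advice helps. If the intention-to-treat result were null, a favourable followed group could be read as evidence for giving children prophylaxis. An unfavourable one could be read as evidence against it. Neither reading would be sound.

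**Working it through.** **The plan's own figure.** Section 10.2 gives 80% power for 1% versus 0.595% with 7,500 per arm. With pooled variance and two-sided 0.05, the mean rate is 0.007975 and

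z = (0.00405 × √7,500 − 1.96 × √(2 × 0.007975 × 0.992025)) / √(0.01 × 0.99 + 0.00595 × 0.99405) = (0.3507 − 0.2465) / 0.1258 = 0.83,

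so power is 79.6%. The figure reproduces. The present point does not depend on it.

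**Inputs from the protocol.** More than 90% of patients are expected to score below 2.5% (sections 6.2 and 7), so at most about 10% are high-risk. That is 750 per arm at 15,000 patients and 2,250 per arm at 45,000.

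**Inputs assumed.** The protocol gives no VTE risk among high-risk patients, no adherence and no strength of selection. Assumed: overall high-risk VTE risk r = 5%; fraction followed f = 0.3 to 0.7; ratio k of the risk in not-followed to that in followed patients = 1.5 to 3; true effect zero.

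**Selection.** With no effect, both arms have the same overall risk:

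r = f × p(followed) + (1 − f) × k × p(followed), so RR(followed vs usual care) = 1 / (f + (1 − f) × k).

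| f | k | Calculation | RR |
|---|---|---|---|
| 0.7 | 1.5 | 1 / (0.7 + 0.45) | 0.87 |
| 0.5 | 2 | 1 / (0.5 + 1.0) | 0.67 |
| 0.3 | 3 | 1 / (0.3 + 2.1) | 0.42 |
| 0.7 | 1/1.5 | 1 / (0.7 + 0.2) | 1.11 |
| 0.5 | 1/2 | 1 / (0.5 + 0.25) | 1.33 |
| 0.3 | 1/3 | 1 / (0.3 + 0.233) | 1.88 |

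The last three rows reverse the selection: the sicker children are the ones whose recommendations are followed. The RR does not depend on r.

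**False positive findings.** A simulation of 200,000 trials per setting, without adjustment, used r = 5% and zero effect. With f = 0.5 and k = 2 the rates are 3.33% followed, 5.00% usual care and 6.67% not followed. Frequency of a significant apparent benefit:

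| Comparison | 750 per arm | 2,250 per arm |
|---|---|---|
| Followed vs usual care | 24% | 62% |
| Followed vs not followed | 55% | 96% |
| Randomized arms, all high-risk | 2.5% | 2.5% |

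Over the whole grid (k = 1.5 to 3), followed versus usual care ranges from 7% to 53% and from 15% to 95%. With k = 1 (no selection) it is 2.0% to 2.4%. A larger trial makes the bias more likely to reach significance.

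**Time before action, alone.** If a share e of VTEs occurs before advice can be acted on, and following is otherwise unrelated to risk, RR = (1 − e) / (1 − r × e). For e = 0.1 this is 0.9 / 0.995 = 0.90; for e = 0.3 it is 0.7 / 0.985 = 0.71. The shares are assumed.

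**Consultants, if consultations after randomization count.** Assume 20% are consulted in either arm at 3% risk, a further 5% are consulted only in the intervention arm at 1.5% risk, and overall risk is 1% in both arms.

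- Consulted: control 3.00%; intervention (0.20 × 3% + 0.05 × 1.5%) / 0.25 = 2.70%; RR 0.90.
- Not consulted: control (1% − 0.6%) / 0.80 = 0.50%; intervention (1% − 0.6% − 0.075%) / 0.75 = 0.43%; RR 0.87.

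Both subgroups look better with no effect. With 2–10% added consultations at 1–2% risk, the ranges are 0.78–0.97 (consulted) and 0.57–0.97 (not consulted).

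**The case against.** Much can be said for the plan.

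- **The analysis is secondary.** Intention-to-treat is primary, and a significance threshold is set only for the primary outcome. This stands: the trial's main conclusion is not at risk. Section 10.1 also names no reference group or test for the three strata, so followed versus usual care is the natural contrast rather than a stated one. But followed versus not followed is confounded in the same way.
- **The direction is open.** A reader might infer that the strata will favour the intervention. The documents do not support that. If teams act most readily on the sickest children, a benefit is hidden. Early discharges falling outside the followed group would do the same, because section 12 collects outcomes only to discharge and short stays leave little time for an event. Contraindicated children cannot be placed with certainty either: they may be not followed, unclassified, or followed if advice to withhold counts.
- **The high-risk comparison by arm is nearly there.** Risk of VTE is a listed subgroup and 0.025 is the cut. This largely stands; what is missing is which score is used and which analysis takes precedence.
- **Subgroup timing may be in the SAP.** A reader might infer that the risk and consultant subgroups are defined after randomization. The protocol does not say so. Section 6.1 provides an admission score in both arms, the nightly update describes the working report, and no text says the team's contact is recorded as a consultation. The consultant bias also needs the intervention to change who is consulted. What stands is that no time limit is set, while both quantities can change during the stay.

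**Conclusion.** The point holds for the as-treated strata. Section 10.1 states this split, so it is not merely a detail left open. It conditions on a decision taken after randomization in one arm only, omits patients with no recommendation, and plans no adjustment between strata. The resulting contrast does not estimate the effect of following the advice.

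The size and sign of the bias are unknown. Under zero effect and the assumed selection, the relative risk for followed versus usual care is 0.42–0.87 one way and 1.11–1.88 the other. These ranges rest on assumed adherence and selection strength. The false-positive rates also rest on the assumed 5% risk and on the largest expected high-risk share.

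For the subgroups, the conclusion is narrower: the risk score and the consultants need a stated measurement time, and would be open to bias if values after randomization were used. The primary intention-to-treat analysis is unaffected.

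**What to change.** Amend section 10.1 as follows:

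1. Make the comparison of randomized arms among patients with an admission score of at least 2.5% the secondary high-risk analysis. Sections 6.1 and 6.3 have scores calculated from admission in both arms and stored for controls, so no new data are needed.
2. Report followed, not followed and no recommendation as three descriptive groups, labelled non-causal.
3. Optionally add a complier-type estimate as a sensitivity analysis. It should not be the required replacement. Section 3 lets the team consider various recommendations beyond anticoagulation, so review may act by other routes, and the exclusion assumption is doubtful and must be stated as such.
4. Use the admission score for the risk-of-VTE subgroup. Limit consultants involved to consultations ordered before randomization, or drop that subgroup.

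The cost is wording plus some loss of scope. The strata can no longer be read as the effect of following the advice. The high-risk estimate by arm is diluted where advice is not followed, and it leaves out children whose score crosses 2.5% only later in the stay.
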